### Statistical analysis

Data cleaning and analysis will be performed using R Studio v3.6.3 statistical software. Outlying data is anticipated as part of potential environmental / technological factors influencing cognitive performance at home and will be excluded utilising Tukey’s Criterion set at three-times the interquartile range. Sensitivity analyses will be performed to determine if participant utilisation of different electronic devices for cognitive tasks influences results. In assessing effects of the autobiographical task, intention to treat and per protocol analyses will be performed.

Comparisons will be made between both arms of the study allocated as per protocol but also across groups utilising blood biomarker status i.e. continuous levels of Aβ, tau, NFL and GFAP.

The study sample size of 50 has 80% power to detect a 7.5% difference in total sleep time and a 5% difference in sleep efficiency and based on PSG obtained normative data [62] allowing for a 10% drop out rate utilising power calculation software [63].

Basic descriptive statistics and demographics will be reported by group for relevant outcomes with appropriate tests for group comparison used depending on data normality assessed by the Shapiro-Wilkes Test.

In addressing the primary hypothesis, sleep outcome measures in Fig. 4 will be sequentially employed as dependent variables in multivariable regression models. Where the same sleep parameter is measured utilising multiple tools, a hierarchical approach will be utilised with EEG data prioritised over actigraphy data without combination of data across measurement tools. Key confounding variables will include age, sex at birth, affective symptoms (GAD-7 total score, GDS total score), medication use (binomial variables for use of each of sedative/hypnotic, antipsychotic, melatonin, ‘Over the Counter’/herbal sleep medications); suspected untreated obstructive sleep apnoea (OSA, STOP-BANG >  = 5 & not on CPAP or known OSA and declined treatment) and specific occupation / employment history (binomial variables for alarm awakening, current shift-work and historic shift-work). Regression models will be checked for adherence to standard assumptions and for multi-collinearity. Clinically plausible non-linear relationships will be assessed by use of stratification and/or quadratic terms with the best-fit model chosen for final presentation with the same approach employed for interaction terms.

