There is a potential for missing data given the study complexity and duration, The approach to this will vary according to the extent and type of data loss. Reported analyses with missing data will make reference to the approach used (anticipated to be simple imputation or complete-case analysis as appropriate). Where possible, sensitivity analyses will be undertaken to examine for any impact of ‘first-night’ effects.

For approaches to identify presence and group-level differences in compensatory sleep and infradian rhythms, see SM 1 – Further Statistical Analysis Data Pertaining to Secondary Hypotheses.

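### The missing-data options named include single imputation, which understates standard errors if it is used to fill in a sleep outcome

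*Protocol article*

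**What the plan says.** The missing-data statement is in the Protocol article, Statistical analysis. It acknowledges that "There is a potential for missing data given the study complexity and duration" and continues that "The approach to this will vary according to the extent and type of data loss". Each report is to state the approach used, which is "anticipated to be simple imputation or complete-case analysis as appropriate". No missing rate is given and simple imputation is not defined.

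Three other parts of the same section matter here:

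- The sample size is 50, "allowing for a 10% drop out rate".
- Each sleep outcome is regressed in turn on a list of confounders. Counted singly there are 12: age, sex, two mood scores, four medication indicators, suspected sleep apnoea, and three alarm and shift-work indicators.
- Where several tools measure the same sleep parameter, the rule is "EEG data prioritised over actigraphy data without combination of data across measurement tools".

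**The concern.** In its usual sense, simple imputation puts one value in each gap and analyses the completed data as if every value had been measured. Done for an outcome, this credits the study with more information than it has. Confidence intervals become too narrow and the test rejects too often.

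Complete-case analysis does not have that fault, but a participant missing any one modelled variable drops out. It also relies on missingness carrying no further information about sleep once arm and covariates are accounted for. That is open to question here. Participants start the headband themselves and complete an electronic diary daily for eight weeks, and Table 1 admits participants with a MoCA as low as 11. MoCA is not among the listed confounders, so severity beyond arm membership is not adjusted for.

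The study already collects several EEG nights and eight weeks of actigraphy per person, so better methods need no new data.

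**Working it through.** **1. The plan's own figure.** With 10% dropout, 45/(1 − 0.10) = 50, so the dropout arithmetic is consistent. The standard deviation and significance level are not given (the effect sizes are "based on PSG obtained normative data"), so the 50 itself cannot be reproduced. Nothing in step 2 depends on it.

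**2. Single imputation of an outcome.** Let n be the number of participants, n_o the number with an observed outcome, m the missing fraction and p the number of coefficients. Regression-imputed values lie exactly on the fitted line. The estimate and the residual sum of squares are therefore those of the observed cases, while the software divides by n − p and uses the design of all n. With outcomes missing at random by chance alone,

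reported SE / true SE ≈ √[ (n_o − p)/(n − p) × n_o/n ], roughly 1 − m.

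Take n = 50 and p = 3 (intercept, arm, one covariate). The two-sided 5% critical value on 47 degrees of freedom is 2.012. The test in effect rejects when |t| on n_o − p degrees of freedom exceeds 2.012 × ratio.

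| Outcomes missing (assumed) | Formula | Ratio | Type I error, formula | Ratio, simulated | Type I error, simulated |
|---|---|---|---|---|---|
| 10% | √(42/47 × 0.9) | 0.90 | 7.8% | 0.89 | 8.2% |
| 20% | √(37/47 × 0.8) | 0.79 | 11.9% | 0.78 | 12.2% |
| 30% | √(32/47 × 0.7) | 0.69 | 17.5% | 0.67 | 18.2% |

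The simulation used 20,000 runs per rate, 25 per arm, one covariate and no arm effect. In the same runs:

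- single imputation with a random residual added gave 7.7%, 10.5% and 14.5%;
- complete cases gave 5.1%, 4.9% and 4.8%;
- filling in the overall mean gave 5.1%, 5.0% and 4.8%.

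The planned model is larger. With 12 covariates, arm and intercept (p = 14), the formula gives √(31/36 × 0.9) = 0.88 at 10% missing and √(26/36 × 0.8) = 0.76 at 20%, so the table does not exaggerate for that model.

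**3. Complete cases: loss of participants.** Arm is always known, so 13 variables can be missing (12 covariates and the outcome). If each is missing independently at rate m, the fraction retained is (1 − m)^13. Starting from 45:

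- 1%: 0.878, about 40 left
- 2%: 0.769, about 35 left
- 3%: 0.673, about 30 left
- 5%: 0.513, about 23 left

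To put this in terms of power, assume a two-sided 5% test with 80% power at 45. The detectable standardised difference is then about 0.855, and unadjusted power for it is 75% with 40 analysed, 69% with 35 and 62% with 30. These rates are illustrations, not estimates for this study.

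**4. Complete cases: validity.** With outcome loss differing by arm (5% against 30%, and 10% against 40%), simulated type I error was 5.0% and 4.9%. Heavier loss in the impaired arm does not by itself distort the arm comparison. Bias needs missingness that still depends on sleep, or on an unmodelled factor related to sleep such as MoCA, after adjustment.

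**The case against.** The strongest reply is that the wording is provisional: methods are anticipated, chosen to suit the data loss and reported each time, and a condensed article may leave the detail to a fuller document. That stands. The lack of a missing rate or a decision rule is therefore not criticised here. What remains is that the article does name its expected methods, and one of them is unsound for outcomes.

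Second, simple imputation might be meant only for isolated covariates or questionnaire items. Mean-filling one covariate left type I error close to 5% in simulation, and overall-mean filling of the outcome also held 5% under the null. This stands too, and it limits the fault to outcomes imputed from arm or regression, with or without a random residual.

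Third, a reader might infer that complete-case analysis would discard much of the sample. The article does not support that. Age, sex and employment are basic demographics, and medication comes from both participants and records, so several items may be almost complete. Independent gaps also spread over more people than clustered ones would. Starting from 45 and then removing people for a missing outcome may count some dropout twice.

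Fourth, a reader might infer that more missing data among impaired participants must bias the comparison. Step 4 shows that it need not.

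Finally, a nightly mixed model does not suit every outcome. Melatonin onset, PSQI, ESS and the sleep regularity index, all in the key to Figure 4, are not nightly measures.

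**Conclusion.** The point holds in a limited form and should be fixed. If single imputation from arm or regression is applied to a sleep outcome, standard errors are understated by about 11% at 10% missing and 22% at 20%, and type I error is about 8% and 12%. This rests on assumed missing rates, chance missingness and a two-sided 5% test. The 18% figure needs 30% of outcomes missing, three times the plan's dropout allowance, and should not be taken as expected.

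Complete-case analysis gives correct standard errors and is valid under the condition in step 4. Its cost in participants is real in principle, but its size is not established by the article. Nor does the article commit the study to an inflated error rate; it leaves open a route to one.

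**What to change.** - State that single imputation will not be used for outcomes.
- Analyse nightly outcomes (for example total sleep time, sleep efficiency, wake after sleep onset, sleep latency) in a linear mixed model with a participant random intercept, using every recorded night retained under the first-night rule. Missing nights then need no imputation.
- For missing covariates, non-nightly outcomes or a wholly missing EEG week, use multiple imputation combined by Rubin's rules. Keep the imputation model small: arm, age, sex, MoCA and, where relevant, actigraphy total sleep time and sleep efficiency.
- Add one line saying that actigraphy serves only as an auxiliary predictor in the imputation, and that this is not the combining of data across tools that the plan excludes.
- Report complete-case results alongside.

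The cost is a paragraph of wording and modest programming, with no new data. The main drawback is that 50 participants and sparse binary covariates can make imputation unstable, which is why the imputation model must stay small.

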## Discussion

This protocol outlines a study scoped to provide novel data concerning the relationship between sleep and AD neurodegeneration both through use of innovative sleep measurement instruments and also through enhanced duration of data collection. We hope to provide new insights into the impact of neurodegeneration on microarchitectural changes in sleep and sleep staging in a home environment. Such insights within the field lend opportunity to improve quality of life for patients but may also allow earlier identification and offer additional treatment targets for intervention.

## Data Availability

The datasets used and/or analysed during the current study are available from the corresponding author on reasonable request.
